## Abstract

**Background**:
Prenatal growth retardation may increase the risk of later chronic non-communicable diseases (NCDs), including diabetes; however, long-term effects of wasting malnutrition in childhood or adulthood are less studied. Pancreatic exocrine and endocrine functions, both critical for nutrition and NCD aetiology, may not fully recover following malnutrition. However, the evidence and mechanistic information is piecemeal. We hypothesise that wasting malnutrition at any age has long-term detrimental effects on endocrine and exocrine pancreatic structure and function.

**Methods: **The SAMPA international research programme will assess pancreatic structure and function in 3700 participants from ongoing observational nutrition cohorts, two adolescent and four adult, in Zambia, Tanzania, Philippines, and India. Pancreas size, structure, and calcification will be assessed by ultrasound and computed tomography (CT) scan; exocrine function by faecal elastase and serum lipase; and endocrine function by haemoglobin A1c (HbA1c) and blood glucose, insulin and C-peptide concentrations during an oral glucose tolerance test (OGTT). In-depth hormonal analyses of incretins, glucagon, proinsulin and trypsinogen during OGTT and intravenous glucose tolerance tests will be done in subsets of adult participants. Pancreatic size and function outcomes will be compared between people with and without prior wasting malnutrition. Analyses will investigate effect modification by sex, current age, time since malnutrition, current body mass index and dietary patterns. Mathematical modelling of OGTT data will be used to estimate the relative contribution to glucose dysregulation of decreased insulin production, changes in insulin clearance and increased insulin resistance. Proinsulin/insulin ratio will be analysed in archived samples from the Tanzanian cohort using a nested case-control design to investigate whether abnormal values precede diabetes.

**Conclusions:** SAMPA, a large-scale multi-centre research programme using data from people with or without prior wasting malnutrition to assess several aspects of pancreatic phenotype, will provide coherent evidence for future policies and programmes for malnutrition and diabetes.

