### Statistical analyses and sample size calculations

Analyses related to individual hypotheses are described below. Primary analyses will be conducted for each cohort separately. Pooled analyses using all or some cohorts combined will be conducted based on the individual cohort results, and in order to investigate how age at malnutrition and length of time between malnutrition and outcome assessment influence the associations between malnutrition and pancreas structure and function. Analyses will be guided by the conceptual framework in
Figure 1. Sample sizes for the specific hypotheses indicate that, with the available number of participants in the cohorts, we have sufficient power for the main analyses with all participants. For some expensive or labour- and participant-intensive outcomes, we had to consider cost and feasibility and have calculated power for analyses in subsets.

*Hypothesis 1:*
Prior malnutrition is associated with later abnormal pancreatic structure and endocrine and exocrine function.

Participants with and without prior wasting malnutrition, the SAMPA study primary exposure, will be compared within each cohort for all pancreas structure and function outcomes: diabetes by OGTT or HbA1c, exocrine function as indicated by faecal elastase and serum lipase, and pancreas size and presence of abnormalities detected by ultrasound or CT scan. We will initially fit regression models for each outcome with prior malnutrition as the main exposure, controlling for sex and for age as a continuous variable. We will investigate whether there are interactions between prior malnutrition and sex, which is known to be associated with both prior malnutrition and diabetes. We will then investigate whether the associations between malnutrition and the outcomes differ by the following variables:
•Time since malnutrition•Sitting/standing height ratio as an indicator of early life stunting•HIV status for African cohorts only (SAM Lusaka, NUSTART Lusaka, CICADA)

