*i.e.* glucose, hormones, faecal elastase and serum lipase, the available sample size in the smallest cohort will be sufficient to determine differences of 0.4 times the standard deviation with 90% power. Expected differences in pancreas volume were calculated using volume normalised to kg body weight to account for the participant age and size range.
^
35
^ A total of n=100 per cohort (assuming a standard deviation of 0.3 mL/kg) will provide 90% power to detect differences of 0.2 mL/kg between those with/without prior malnutrition, which is a smaller difference than that expected between people with and without diabetes.
^
35
^
^,^
^
36
^

*Hypothesis 2:*
Prior malnutrition is associated with pancreatic calcification which in turn is associated with diabetes.

To investigate whether prior malnutrition is associated with pancreas calcification, from each adult cohort we will randomly select for CT scans 50 participants who were exposed to malnutrition and 50 controls who were not exposed. The presence of calcification or other pancreas abnormalities on CT will be compared between those with or without prior malnutrition.

In order to increase sample size for this and for the second part of the hypothesis comparing calcification with diabetes, results from CT scans in the subset of participants with these will be compared with the ultrasound results from the same participants to indicate whether abnormalities determined by ultrasound, e.g. pancreas body or duct shape, correspond to calcification by CT scan. We will then compare the proportion of abnormalities based on ultrasound or CT scan among those with and without diabetes.

**
*Sample size*
**: Population prevalence estimates for pancreatic calcification appear unavailable so we have not performed any sample size calculations. Pancreatic calcifications are seen in fibro-calculous pancreatic diabetes
^
7
^ but these studies have been conducted on participants selected for their clinical presentation.

*Hypothesis 3:*
The abnormal glucose regulation seen after malnutrition is associated with relative insulin deficiency with or without insulin resistance.

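### Hypothesis 2 tests calcification cohort by cohort on 50 v 50 CT scans and leaves pooling to depend on those results; one stratified analysis of all four adult cohorts should be fixed in advance.

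*Protocol article*

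**What the plan says.** All of this is in the protocol article, mostly under Statistical analyses and sample size calculations.

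- **Sample.** Under Hypothesis 2, "from each adult cohort we will randomly select for CT scans 50 participants who were exposed to malnutrition and 50 controls who were not exposed". In the Abstract the cohorts are counted as "two adolescent and four adult", so the CT sample is 4 × 50 = 200 exposed and 200 unexposed.
- **Unit of analysis.** The section opens with "Primary analyses will be conducted for each cohort separately".
- **Pooling.** "Pooled analyses using all or some cohorts combined will be conducted based on the individual cohort results". Its other stated purpose is to study age at malnutrition and time since malnutrition.
- **Precision.** "Population prevalence estimates for pancreatic calcification appear unavailable so we have not performed any sample size calculations". No detectable difference, interval width or scenario range follows. The section's opening paragraph says that for costly outcomes the authors "have calculated power for analyses in subsets". That is so for pancreas volume in the CT subset, but not for calcification in the same subset.
- **Ultrasound.** "In order to increase sample size for this and for the second part of the hypothesis comparing calcification with diabetes", CT findings will be compared with ultrasound in the same participants, to see whether ultrasound abnormalities correspond to calcification.

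Under Outcome measures, calcification by CT is a secondary outcome.

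**The concern.** Hypothesis 2 concerns prior wasting malnutrition in general, and the overall hypothesis covers malnutrition at any age. The primary comparison nevertheless divides 400 scans into four sets of 100 for a finding that may be uncommon. If calcification affects a few per cent of exposed adults, each cohort will probably be non-significant whether or not the hypothesis is true.

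The analysis that could detect such a difference is the pooled one. Whether it is done, and which cohorts enter it, is tied to cohort results already seen. A pooled p-value obtained that way no longer has its nominal error rate, and a decision not to pool after four nulls would leave the question unanswered.

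Unknown prevalence is a reason not to give a single power figure, but it does not rule out a range. Under Hypothesis 1 the article meets the same difficulty for glucose intolerance (2% to 11% in the never malnourished), assumes 7%, and states power.

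**Working it through.** **Inputs from the article.** 50 v 50 per adult cohort; four adult cohorts; cohort-separate primary analysis; for volume in the same CT subset, SD 0.3 mL/kg, difference 0.2 mL/kg, 90% power.

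**Assumptions not in the article.** Fisher's exact test, two-sided 5%; control prevalence 0% to 5%; every scan readable; 80% power as the benchmark, which the article uses for its binary glucose outcome.

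**1. The article's own figure for the CT subset.** There is no calcification figure to reproduce. The volume figure does reproduce: n per group = 2 × (1.96 + 1.282)² × 0.3² / 0.2² ≈ 47.3, or 48 after rounding up. With 50 per group, power is 91.5%.

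**2. What counts reach significance in one cohort.** With no calcification in controls, the two-sided Fisher p for k v 0 is 2 × C(50,k)/C(100,k).
- k = 5: 2 × 2,118,760 / 75,287,520 = 0.056.
- k = 6: 2 × 15,890,700 / 1,192,052,400 = 0.027.

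So at least 6 of 50 (12%) is needed against none. Against 1 control case, 8 of 50 is needed.

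**3. Exposed prevalence needed for 80% power** (exact binomial enumeration, Fisher):

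| Control prevalence | One cohort, 50 v 50 | Four cohorts, 200 v 200 |
|---|---|---|
| 0% | 15.4% | 3.9% |
| 1% | 18.1% | 6.5% |
| 2% | 20.5% | 8.4% |
| 5% | 26.4% | 13.4% |

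The choice of test matters. With an uncorrected chi-square the 50 v 50 column becomes 10.8%, 14.7%, 17.4% and 23.3%.

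**4. Power at one modest difference, 6% v 0%.** With no control cases, power is P(X ≥ 6), because 6 v 0 is also the smallest significant result at 200 v 200 (p = 0.030).
- One cohort, X ~ Bin(50, 0.06): 7.8%, about 8%.
- If that difference held in all four cohorts, the chance that all four are non-significant is (1 − 0.078)⁴ ≈ 72%.
- All four together, X ~ Bin(200, 0.06): 98%.

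**5. What a group with no calcification would exclude.** The upper limit for 0 of n is 1 − 0.05^(1/n) one-sided, or 1 − 0.025^(1/n) as the limit of a two-sided 95% interval.
- n = 50: 5.8% and 7.1%.
- n = 200: 1.5% and 1.8%.

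The 200 v 200 figures are unadjusted and not stratified.

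**The case against.** **The article discloses the gap, and the outcome is secondary.** Both are true. In a condensed article a missing precision sentence would be only missing detail. What remains is what the article does state: a cohort-separate primary analysis, with pooling conditional on its results.

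**Detectable differences depend on the unknown control prevalence.** This stands. For one cohort the threshold runs from 15.4% to 26.4% as controls go from 0% to 5%, and it falls to 10.8% with chi-square and controls at 0%. Only the upper limits for a zero count are free of that input. The answer is to state a range.

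**The article plans two ways to enlarge the sample.** It does, so 50 v 50 CT is not the whole of the evidence. Pooling, however, is conditional on the cohort results. Ultrasound is planned for all participants and records calcification, but extending the sample with it rests on CT-ultrasound correspondence, which needs calcified CT cases to establish. The comparison then spelled out is by diabetes status.

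**Pooling has real costs.** The cohorts differ in age at malnutrition, time since malnutrition and infection. In NUSTART Lusaka all exposed participants are HIV-infected, while half of the 100 planned controls are not. Stratifying by cohort does not remove that imbalance. A bare exact test would also drop the age and sex adjustment planned under Hypothesis 1. These points shape the fix but do not remove the need for it.

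**A stronger reading is tempting:** that the comparison can succeed only if about one in six exposed adults has calcification. The article does not support it. One in six is roughly an 80%-power threshold with controls near 0% to 1%; 6 v 0 (12%) is already significant, and power reaches 50% at 11.3% (controls 0%) or 13.0% (controls 1%). Nor does the article say that cohort nulls will be read as evidence against an analogy with fibro-calculous diabetes. That is a risk of misreading only.

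**Conclusion.** The point holds in a limited form. The primary calcification comparison uses a unit of analysis that can reliably detect only large differences: about 15% to 20% exposed prevalence for 80% power with controls at 0% to 2%. The more sensitive analysis of the same scans is left to depend on the cohort results. At 6% v 0%, the choice between one cohort and all four moves power from 8% to 98%. This rests on Fisher's exact test at two-sided 5%, low control prevalence and readable scans, and the pooled figure also assumes a similar effect in all four cohorts.

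No printed figure is wrong, and the volume calculation for the same subset is right. This is an improvement that should be made before the CT results are examined.

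**What to change.** 1. Specify in advance that the malnutrition-calcification test is one analysis of all four adult cohorts (200 v 200), stratified by cohort, using an exact or penalised logistic model that keeps the age and sex adjustment.
2. Add an HIV-adjusted or HIV-restricted sensitivity analysis where exposure and HIV are imbalanced, as in NUSTART Lusaka.
3. Show cohort-specific estimates and intervals alongside, so that differences by age at malnutrition or infection remain visible.
4. Replace the sentence that no calculation was done with what the counts can show: unadjusted 80% power pooled at about 4%, 6.5% or 8.4% exposed prevalence with controls at 0%, 1% or 2%; and, if a group shows no calcification, upper 95% limits of 1.5% to 1.8% pooled (0/200) and 5.8% to 7.1% per cohort (0/50), one-sided to two-sided.
5. Keep the ultrasound extension as planned, and say that it depends on CT-ultrasound correspondence and does not replace this test.

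The cost is wording and one prespecified model, with no new scans. The downside is that a pooled test assumes a broadly common direction of effect across cohorts that differ in age at malnutrition and in infection; if effects run in opposite directions, it loses power.

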**3.**	** *CICADA (Chronic Infections, Co-morbidities and Diabetes in Africa), Mwanza, Tanzania* ** The CICADA cohort, ^ 17 ^ total n=1947, comprises three subgroups: a) Tuberculosis patients and controls from the TB-NUT study whose HIV and nutritional status ~16 years ago at recruitment are known (50% BMI<18.5 kg/m ^2^) as well as more recently recruited HIV-infected and uninfected people (controls) ^ 18 ^ ^,^ ^ 19 ^ b) NUSTART, conducted 2010-2014, was a two-site (Mwanza and Lusaka) trial of food supplements for malnourished (BMI<18.5 kg/m ^2^) HIV-infected adults, recruited when starting antiretroviral therapy. ^ 20 ^ In Mwanza, 704 participants were recruited, 409 were alive and followed at the 12-week NUSTART end-point; 273 were available at a follow-up two-three years after starting ART and 206 were recruited to the CICADA study. c) HIV-infected and uninfected people, both malnourished and well-nourished, recruited 3-four years ago for HIV, nutrition and diabetes assessments *CICADA has the most detailed longitudinal diabetes data of the project cohorts, archived fasting samples, and are the oldest so have had longer to develop diabetes; therefore, this cohort will be used for the in-depth and longitudinal components.*	CICADA (TB-NUT) 16 y prior: 450 total • 73 (16.2%) BMI <17 kg/m ^2^ • 74 (16.4%) BMI 17 to 18.5 kg/m ^2^ • 303 (67.4%) BMI > 18.5 kg/m ^2^ CICADA (NUSTART) 11 y prior: 208 total • 105 (50.5%) BMI <17 kg/m ^2^ • 103 (49.5 %) BMI 17 to 18.5 kg/m ^2^ CICADA (New HIV +/- cohort) 4 y prior: 1293 total • 109 (8.4%) BMI <17 kg/m ^2^ • 171 (13.3 %) BMI 17 to 18.5 kg/m ^2^ • 1009 (78.3%) BMI >18.5 kg/m ^2^ Expected for SAMPA: 1412 total
**4.**	** *NUSTART, Lusaka, Zambia* ** 200 previously malnourished HIV-infected adults will be traced and recruited from the NUSTART Lusaka participants. ^ 20 ^ We will also recruit 50 HIV-infected and 50 non-HIV-infected, not previously malnourished, neighbourhood controls.	• 10 y prior: 1111 total, 437 (39%) BMI 17 to 18.5 kg/m ^2^, 674 (61%) BMI<17 kg/m ^2^ • Expected for SAMPA: 300 total

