A deeper understanding of associations between prior malnutrition and the underlying glucose metabolic pathways will be explored through modelling biochemical measures over the course of the two-hour OGTT. Glucose, insulin and C-peptide data from OGTT will be used to model pancreatic cell functionality according to published methods in order to determine a set of indices quantifying: first phase, second phase, and total insulin secretion,
^
37
^ whole-body and hepatic insulin clearance,
^
38
^ and insulin sensitivity.
^
25
^
^,^
^
39
^ For the child cohorts for whom only three blood samples are available over the two-hour OGTT, we will use methods designed to determine insulin sensitivity from sparsely sampled OGTTs.
^
26
^ The IVGTT data from the CICADA cohort subset can be similarly modelled to estimate insulin sensitivity and insulin secretion. Comparison of the indices estimated from the two tests will provide information as to whether altered intestinal function,
*e.g.* glucose absorption or incretin secretion, influences insulin secretion or sensitivity in participants previously malnourished or not.

**
*Sample size*
**: We will use individual data from all SAMPA adult participants and, for children who have only three sample points during OGTT, we will combine data from groups of participants.
^
26
^ Most previous studies in this area include 10-100 people per group, whereas we will be able to study all SAMPA participants.

*Hypothesis 4:*
An abnormal fasting pro-insulin/insulin ratio is associated with later development of diabetes in adults who had malnutrition and infection.

**
*Analysis*
**: We will use the detailed data and samples available from CICADA to investigate whether the proinsulin/insulin ratio in CICADA samples collected from fasted participants about four years prior to the SAMPA visit is associated with diabetes or prediabetes at the SAMPA visit. This will be a nested case-control study where cases are 60 CICADA participants with current diabetes by OGTT and controls are 60 CICADA participants with normal OGTT. These participants will be selected by stratified random sampling. Logistic regression will be used, controlling for age and sex, to determine if prior proinsulin/insulin ratio is associated with later diabetes.

**
*Sample size*

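### The Hypothesis 4 case definition does not exclude diabetes already present when the archived sample was drawn, so a positive result could not separate a forerunner of diabetes from a companion of it

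*Protocol article*

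**What the plan says.** The aim concerns order in time. The Abstract describes the work as "using a nested case-control design to investigate whether abnormal values precede diabetes". Hypothesis 4, in the statistical analyses section, reads: "An abnormal fasting pro-insulin/insulin ratio is associated with later development of diabetes in adults who had malnutrition and infection".

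The exposure is the ratio in archived CICADA samples, and the analysis sentence asks whether the ratio in samples "collected from fasted participants about four years prior to the SAMPA visit is associated with diabetes or prediabetes at the SAMPA visit".

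The sampling rule uses status at the SAMPA visit only: "cases are 60 CICADA participants with current diabetes by OGTT and controls are 60 CICADA participants with normal OGTT". On selection, the article adds: "These participants will be selected by stratified random sampling". It does not name the strata. On the model: "Logistic regression will be used, controlling for age and sex, to determine if prior proinsulin/insulin ratio is associated with later diabetes".

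The sample size paragraph claims 90% power with 120 samples, 1:1, for a ratio difference of 0.04 with SD 0.07. It notes that this difference is smaller than the one reported between people with and without type 2 diabetes, and that the number was set by available cases and cost.

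Table 1 says that CICADA holds the most detailed longitudinal diabetes data of the cohorts. One of its subgroups was "recruited 3-four years ago for HIV, nutrition and diabetes assessments".

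**The concern.** Under the stated rule, a person who already had diabetes when the archived sample was drawn, and still has it, qualifies as a case. For that person an abnormal archived ratio accompanies existing disease and says nothing about what came before it. Adjusting for age and sex does not remove this. The case group may therefore mix incident and prevalent diabetes, and the comparison cannot tell the two explanations apart. That distinction is the whole content of Hypothesis 4.

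There is also a smaller inconsistency. The analysis sentence asks whether the ratio "is associated with diabetes or prediabetes at the SAMPA visit", but cases are defined by diabetes and controls by a normal OGTT. Participants with prediabetes then fall in neither group.

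**Working it through.** **1. Aim against sampling rule.** The Abstract and Hypothesis 4 speak of preceding and later development. The case definition, and the last secondary outcome in the outcomes list, use current diabetes by OGTT. No section sets a condition on glycaemic status at the archived-sample visit, for cases or for controls. Controls with a normal OGTT now are less likely to have had diabetes then, so the problem lies mainly with the cases.

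**2. The plan's own power figure.** Inputs from the sample size paragraph: 60 per group, difference 0.04, SD 0.07. Alpha is not stated; two-sided 5% is assumed.

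- Standard error = 0.07 × √(1/60 + 1/60) = 0.01278.
- 0.04 / 0.01278 = 3.13.
- Power = 87.9% by the normal approximation, or 87.4% by the noncentral t.

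This is slightly below the stated 90%. A difference of 0.0414 would give 90%, so rounding explains the gap. The point here does not depend on it.

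**3. What prevalent cases alone could produce.** Let f be the share of the 60 cases already diabetic at the archived visit. Let D be the ratio difference in established diabetes. Set the true difference before onset to zero. The expected observed difference is then f × D, and the chance of a significant result in the expected direction is the noncentral t power at f × D with SD 0.07 and 60 v 60. Neither f nor D is given. The article says only that the published difference exceeds 0.04, so D of 0.05 to 0.08 is an assumption, and so is every f.

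| f | f × D (D = 0.05) | Chance significant | f × D (D = 0.08) | Chance significant |
|---|---|---|---|---|
| 10% | 0.005 | about 6% to 7% | 0.008 | about 9% to 10% |
| 25% | 0.0125 | 16% | 0.020 | 34% |
| 50% | 0.025 | 49% | 0.040 | 87% |

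In the 10% row the higher figure also counts results significant in the opposite direction; in the other rows this makes no material difference. Holding the SD at 0.07 ignores the wider spread of a mixed case group. Allowing for it lowers the figures slightly, for example from 34% to about 31% and from 87% to about 82% at D = 0.08.

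**4. Power after restricting to incident cases.** Keep 120 assays, difference 0.04, SD 0.07, two-sided 5%, noncentral t. The standard error is 0.07 × √(1/cases + 1/controls).

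| Incident cases v controls | Standard error | Power |
|---|---|---|
| 60 v 60 | 0.0128 | 87% |
| 45 v 75 | 0.0132 | 85% |
| 30 v 90 | 0.0148 | 77% |
| 15 v 105 | 0.0193 | 54% |

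**The case against.** The article is condensed. It calls the study nested, speaks of later diabetes, points to CICADA's longitudinal data and leaves the strata unnamed. A baseline criterion or a sensitivity analysis could sit in a fuller document. This has some force: the article is silent on baseline status and does not say that prevalent cases are wanted. It does, however, state the case definition, control definition, numbers, model and covariates, and the definition it states admits prevalent diabetes. Calling the design nested does not change who qualifies as a case.

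Two stronger readings are tempting, and the documents support neither.

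- A reader might infer that the study cannot show precedence at all. The share of prevalent cases is unknown. At 10% the false-positive chance is only about 7% to 10%, and CICADA appears to hold the data needed to remove the problem.
- A reader might infer that controls with a normal OGTT inflate the odds ratio. Comparing diabetes with normal glucose tolerance is an openly stated contrast. Leaving out the intermediate group changes what the odds ratio estimates; it is not an error in itself.

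It is also fair to say that the remedy may cost more than a trivial loss of power, since the number was tied to available cases, and that this is the last secondary outcome in a 120-person subset of one cohort.

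**Conclusion.** The point holds in this form: the stated case definition does not exclude diabetes present at the archived-sample visit, and nothing in the stated model compensates. A positive result would therefore not answer the question that Hypothesis 4 asks.

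The size of the bias cannot be fixed from the documents. Across the assumed shares of 10% to 50% and an assumed D of 0.05 to 0.08, it runs from close to the nominal 5% to a very likely false positive. These percentages illustrate the mechanism and do not estimate what will happen in CICADA. The mismatch between an outcome that includes prediabetes and a case definition that does not is real but secondary. The primary outcomes and the other hypotheses are not touched.

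**What to change.** 1. Draw both cases and controls only from CICADA participants without diabetes at the visit when the archived sample was taken, using the glycaemic data held from that visit. State the criterion, and how prediabetes at that visit is handled.
2. Count the incident cases before any archived sample is used. If there are fewer than 60, take all of them, fill the 120 assays with controls, and restate power from the second table in the working.
3. Make the outcome sentence and the case definition agree: either diabetes only, or diabetes plus prediabetes, in both places.

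The cost is a selection filter and the same 120 assays. This assumes that glycaemic status at the archived visit is on file for those sampled. Table 1 suggests so but does not say it for every participant. The downside is possibly fewer cases and lower power, small at 45 incident cases (85%) but substantial at 15 (54%).
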